#### Analyses

All primary and secondary outcomes will be analysed using the "Intention to treat" principle. A comparison of key endpoints will be made for mothers in all three groups. Analyses will be performed with a researcher blinded to group allocations. Initial analyses will examine baseline characteristics of all randomised participants as per the intention to treat principle. If chance differences in baseline data are found between treatment groups, these will be taken into account in subsequent analyses. The population will be characterised by maternal age, highest level of education, maternal expectations of a normal delivery and parity.

#### Statistical tests

Descriptive statistics Mean/sd for parametric data, Median and inter-quartile range for non-parametric data. For Dichotomous outcomes: Chi squared/Relative Risks with 95% confidence intervals. Regression analysis will be utilised to examine the influence of potential confounders on our outcomes of interest. NNT for benefit and harm where appropriate will be calculated.

#### Sub-group analyses

Subgroup analyses of primary outcomes will be performed for women regarding; induced vs spontaneous labour; attendance at all three sessions, whether each session cd was used at least once; size of group < 3 women, hypnotist, women's hypnotisability as measured by the CIS, women's beliefs; on whether they were in experimental group, women's beliefs of the efficacy of hypnosis prior to labour, Women's expectations of requiring an epidural, Women's expectations of having a normal spontaneous birth, Previous experience of non childbirth hypnosis or yoga. hypnotisability as measured by the Creative Imagination Scale. Some women will not attend the sessions to which they are allocated. We have tailored the hypnosis intervention so that most of the skills are learned in the first session and nearly all the skills are delivered by the second session. The third session is for re-enforcement and consolidation. Any women giving birth prior to completing all three sessions will be analysed both on an "intention-to-treat" basis and with total session exposure as a predictor.

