#### Multiparous vs nulliparous

Previous randomised comparisons of hypnosis in this setting have investigated nulliparous women only. Two hypnosis studies investigating multiparous women used parity matched controls. These reports show similar (but reduced) treatment effects in favour of hypnosis [37,47].

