### Group 3: No intervention control

Women allocated to usual care will not be asked to attend any further sessions at the hospital other than those required for their usual antenatal care. The next involvement of these mothers will be in responding to a maternal questionnaire in the early postnatal period.

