#### Blinding

The nature of the intervention makes it difficult to double blind comparisons between hypnosis groups and non intervention controls. However every attempt will be made to conceal treatment allocations from obstetricians, anaesthetists, midwives and those personnel collecting and analysing data. All participants will be informed that they may or may not appreciate which group they are in. Women allocated to usual care will probably realise they are not in an intervention group. Although it may not be possible to blind the administration of our intervention, all data will be collected and analysed by researchers who will be unaware of the participant's group allocation. Any comparisons of participants receiving an intervention in Groups 1 and 2 will be in a true double blind fashion with both participants and outcome assessors blinded to allocation. Our primary outcomes and key secondary outcomes are designed to be as objective as they can be for a study of this type. An assessment of blinding will be determined by asking participants if they thought they were in a control or intervention group in the final post-partum questionnaire.

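### Six of the eleven planned subgroup factors are set after randomisation, four of them do not exist under usual care, and parity is not on the list

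*Protocol article*

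**What the plan says.** The Sub-group analyses section of the protocol article applies its list to the primary outcome. It opens with "induced vs spontaneous labour" and continues with "attendance at all three sessions, whether each session cd was used at least once; size of group < 3 women, hypnotist". It then names hypnotisability on the Creative Imagination Scale (CIS, entered twice), belief about allocation, belief in hypnosis, expectations of an epidural and of a normal birth, and earlier non-childbirth hypnosis or yoga. Women who deliver before finishing the sessions are analysed by intention to treat "and with total session exposure as a predictor".

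Three other sections bear on this list:
- **Group 3: No intervention control:** "Women allocated to usual care will not be asked to attend any further sessions at the hospital", beyond usual antenatal care.
- **Blinding:** belief about allocation is obtained by "asking participants if they thought they were in a control or intervention group in the final post-partum questionnaire".
- **Multiparous vs nulliparous**, on two parity-matched studies that included multiparous women: "These reports show similar (but reduced) treatment effects in favour of hypnosis". The Background adds that primiparous women appear more responsive to hypnosis.

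Randomisation is stratified by parity, and the Analyses section uses parity to describe the population. Parity is not among the subgroup factors.

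**The concern.** A subgroup effect keeps the protection of randomisation only if the subgroup is defined by something fixed before allocation. Otherwise the women in the subgroup may differ between arms for reasons unrelated to the treatment effect. If a factor exists only in the hypnosis arms, any contrast with usual care sets selected women against unselected ones. If a factor is measured after the outcome, the outcome can decide who belongs to the subgroup.

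At stake is how the secondary results are read. A gradient across attendance or number of sessions is easily taken as dose-response, and selection alone can produce one. The listed analyses would also not show whether the effect differs by parity, which the trial stratifies on and has reason to examine.

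**Working it through.** **1. When each factor arises, and whether Group 3 has it**

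| Factor | Timing | Defined in Group 3? |
|---|---|---|
| Onset of labour (induced or spontaneous) | after allocation | yes |
| Attendance at all sessions | after allocation | no |
| CD use | after allocation | no |
| Session group size | after allocation | no |
| Hypnotist | after allocation | no (Group 1 only) |
| Believed allocation | after the birth | yes |
| CIS hypnotisability | baseline | yes |
| Expectation of a normal birth | read as baseline | yes |
| Earlier hypnosis or yoga | baseline by nature | yes |
| Belief in efficacy | not stated, except that it precedes labour | yes |
| Expectation of an epidural | not stated | yes |

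Six of 11 (55%) arise after randomisation. If both factors of unstated timing were measured after allocation, it would be 8 of 11 (73%). Four of 11 (36%) are undefined under usual care.

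**2. Session exposure.** Sessions are weekly for three weeks, starting as near as possible to 37 weeks. Entry runs to just under 39 weeks. Birth therefore caps the number of sessions, and planned inductions move the schedule (Treatment schedules). Session count carries gestation at birth, induction and willingness to attend.

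**3. Selection with no treatment effect (illustration).** Assume half the women use analgesia at 70% and half at 90%. The overall rate is then 80%, as in the audit in the Power calculation. Let full attendance be 80% in the first half and 60% in the second.
- Attenders: (0.5×0.8×0.70 + 0.5×0.6×0.90) / (0.5×0.8 + 0.5×0.6) = 0.55/0.70 = 78.6%.
- Non-attenders: (0.5×0.2×0.70 + 0.5×0.4×0.90) / (0.5×0.2 + 0.5×0.4) = 0.25/0.30 = 83.3%.
- Controls: 80%.

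| Attendance in the two halves | Attenders | Non-attenders |
|---|---|---|
| 75% and 65% | 79.3% | 81.7% |
| 80% and 60% | 78.6% | 83.3% |
| 90% and 50% | 77.1% | 86.7% |

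In each row attenders look better than controls and non-attenders look worse, although hypnosis does nothing.

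**4. Number of factors.** Eleven independent tests at 5% on one contrast give 1 − 0.95^11 = 0.431. This is an upper illustration. Attendance, CD use and onset of labour are related, and the article sets no test level for subgroups.

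**5. What adding parity would offer.** The plan's own sizing reproduces first. For 80% against 64%, two-sided 0.05 and 80% power, the continuity-corrected formula gives 135 per group (123 uncorrected), and 135/0.90 = 150.

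Now assume an even parity split, so 67.5 women per arm and stratum. Let the fall be 16 points in one stratum and 8 in the other (normal approximation, risk-difference scale, no continuity correction).
- SE = √[(0.80×0.20 + 0.64×0.36)/67.5 + (0.80×0.20 + 0.72×0.28)/67.5] = √(0.7520/67.5) = 0.1056.
- Power = Φ(0.08/0.1056 − 1.96) = Φ(−1.20) ≈ 11%.
- If the effect is nil in the second stratum, power is about 34%.

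**The case against.** The strongest defence is that intention to treat governs every primary and secondary outcome, and that the exposure analysis is added to it. A reader might infer that the main result is compromised, or that the plan commits itself to causal dose-response claims. The article supports neither reading.

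Nor does it name the comparator for each subgroup. Attendance, CD use and group size exist in both hypnosis arms, so the list could be meant for Group 1 against Group 2 or for description within arms. That stands. A contrast of attenders with all controls is one reading of the list, not a stated commitment. But attendance and CD use still follow allocation and may be selected differently in a hypnotherapist-led and a nurse-led group, and the section does not mark any of these analyses as exploratory.

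On parity, a reader might infer that it is the only modifier the article supports. It is not. The Discussion grades people by hypnotic responsiveness, and the list includes CIS, which is measured at baseline in all arms. Parity could also enter the planned regression, and Additional file 1, which is not shown, may hold parity hypotheses. Adjustment, however, does not estimate effect modification, and the explicit list omits parity.

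Some inductions are planned before the sessions and so are foreseeable, but the listed factor is how labour began.

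It is also tempting to put a figure on the women whose date of birth rules out three sessions. The article gives no distribution of gestation at entry or birth, so such a figure would depend on assumptions and none is offered here.

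**Conclusion.** The point holds for the subgroup and exposure analyses and does not touch the primary comparison. Six of the eleven factors follow randomisation, a bare majority. Four are undefined in usual care, and one is recorded after the outcome. Parity is absent although it is the stratifier and a suggested modifier.

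The count rests on the text alone. The size of the bias does not. In the illustrations, full attenders fall 0.7 to 2.9 points below controls with no effect, under assumed prognosis and attendance rates. That is small beside the 16-point planning difference, but the attender to non-attender gap of 2.4 to 9.6 points could pass for dose-response. The 43% chance of a false finding is an upper illustration under independence. The change is worth making before analysis.

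**What to change.** 1. Restrict effect-modification analyses to factors fixed before randomisation. Put parity and CIS first, then earlier hypnosis or yoga, and expectations and beliefs only if recorded before allocation; state when each is recorded. Report each as a treatment-by-factor interaction estimate with its confidence interval.
2. Report attendance, CD use, session exposure, group size and hypnotist as exploratory, non-causal descriptions within the hypnosis arms (hypnotist in Group 1 only). Drop actual onset of labour as an effect modifier.
3. Use believed allocation only for the blinding check.
4. If an effect of receiving treatment is wanted, estimate a complier-average effect with randomisation as the instrument, and define compliance as any receipt (at least one session or a posted CD). Completion of all three sessions would be unsound as the definition: the article says most skills come in the first session, and CDs of missed sessions are posted, so partial attenders are substantially treated. State the assumptions, in particular that allocation acts only through receipt.

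The cost is a change of wording, with no new data and no change to the sample size. A parity interaction has only about 11% power if the effect halves in one stratum (even split assumed), so it should be read as an estimate rather than a test. The complier estimate is less precise than a naive per-session comparison.

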#### Interim sequential analyses

Interim sequential analyses as described by Whitehead[64] are planned for all primary and main secondary outcomes when 150 and 300 participants have been recruited. Our independent data monitoring committee (DMC) has clear stopping rules in their terms of reference when reviewing data and will perform analyses as Group A vs B vs C without knowing which group is intervention or control. Stopping rules will include: a significant difference in serious adverse events between groups; clear differences (p < 0.01) between groups shown in primary outcome, and futility in continuing the trial is established. If these criteria are not met the interim sequential analyses will not be revealed to the researchers until the end of the trial. If this is the case the Steering Committee will be informed of the DMC recommendations.

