#### Power calculation

It is proposed that sufficient women be randomised to provide reliable evidence of the effects of antenatal hypnosis regarding the primary outcome measure of this study: the incidence of not using pharmacological pain relief during labour. An audit of 100 consecutive mothers birthing at the Women's and Children's Hospital in May 2004 showed an incidence of using one or more pharmacological interventions of 80%. In order to show a clinically relevant fall of 20% in the number of women requiring pharmacological analgesia ie from 80% to 64%. Using a 2 tailed calculation (Nquery advisor computer program V.5) a study with 80% power would require each group to contain 135 women to detect this difference at the 0.05 level.

Complete collection of the primary endpoint is likely as all analgesia techniques used such as Entonox, pethidine and epidural analgesia are documented routinely in the labour ward birth register and medical record by the woman's treating midwife. We plan to recruit 150 women/group as we estimate that 10% of participants' will deliver prior to receiving their allocated treatment. The findings of our case matched control study at the Women's and Children's Hospital[47] are consistent with those of our systematic review of the literature on this topic [22]. No comparative trials have investigated the effects of hypnosis on the incidence of postnatal depression although acknowledged experts in the field report a low incidence in women taught hypnosis (<1%) [21]. The prevalence of post-natal depression in several recent studies in Australia is between 13 and 18% [63]. Our proposed study has a power of 80% at the 0.05 level of significance to show a reduction from 16% to 5.4% for this secondary outcome. For normally distributed continuous measures (eg EPDS) we would be able to detect shifts of 0.4 SD with a power of 80 % between individual arms of the study (n = 135 per group). Comparisons which exploit the two treatment groups (assuming a conservative estimate of postnatal data in 270 subjects in Groups 1 and 2) would have 80% power to detect a shift of only 0.28 SD.

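### The flat p<0.01 interim stop and the sample size at an unreduced 0.05 do not fit together: if the final test is at 0.05, error is about 5.9% for one contrast or a three-arm test.

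*Protocol article*

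**What the plan says.** All references are to the protocol article.

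- **Interim sequential analyses.** The article cites a published sequential method and says that such analyses "are planned for all primary and main secondary outcomes when 150 and 300 participants have been recruited". The stopping rules include a difference in serious adverse events, then "clear differences (p < 0.01) between groups shown in primary outcome, and futility in continuing the trial is established". The data monitoring committee works with coded groups A, B and C and has its own terms of reference, which are not shown. No numerical threshold is given for futility.
- **Power calculation.** "In order to show a clinically relevant fall of 20% in the number of women requiring pharmacological analgesia ie from 80% to 64"%; the study "would require each group to contain 135 women to detect this difference at the 0.05 level", two-tailed. Recruitment is raised for women who deliver early: "We plan to recruit 150 women/group as we estimate that 10% of participants' will deliver prior to receiving their allocated treatment".
- **Analyses** and **Statistical tests.** "A comparison of key endpoints will be made for mothers in all three groups". Dichotomous outcomes get chi-squared tests and relative risks with 95% confidence intervals. No single primary contrast is named.
- **Additional specific aims.** Comparing the two ways of delivering hypnosis (Group 1 v Group 2) is an aim in its own right.

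**The concern.** A formal sequential design links three things: the interim boundaries, the final critical value and the sample size. Here the boundary is a flat p<0.01 at one third and two thirds of recruitment, while the sample size belongs to a trial with one analysis at 0.05. Chances to reject at the two looks, added to a full 0.05 at the end, bring the total above 5%.

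The article also leaves open what a difference between groups means at a look. It could be one test across three arms, a hypnosis v control contrast, or any pair. On the last reading, a difference between the two hypnosis arms alone could end the trial without settling whether hypnosis beats usual care.

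A smaller point is that the looks are triggered by recruitment. Women enter after 34 weeks and the primary outcome is known only at birth, so the latest recruits will not yet have an outcome. The data at a look will then be somewhat short of 50 or 100 women per arm.

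**Working it through.** **1. Reproducing the plan's figure.** Inputs from Power calculation: 80% v 64%, two-sided 0.05, 80% power. The mean rate is 0.72 and the difference 0.16.

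n = [1.960·√(2·0.72·0.28) + 0.842·√(0.80·0.20 + 0.64·0.36)]² / 0.16² = 3.134 / 0.0256 = 122.4, that is 123 per group.

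With continuity correction: (n/4)·[1 + √(1 + 4/(n·0.16))]² with n = 122.4 gives 134.6, that is **135**. Then 135/0.90 = **150**. Both stated numbers are reproduced, and the 10% uplift is used up by early delivery. Nothing is left for interim looks or for a third arm.

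**2. Error under no effect.** Simulation of 1,000,000 trials with 80% use in all arms and outcomes known for 50, 100 and 150 women per arm. The test is p<0.01 at looks 1 and 2 and p<0.05 at the end, with futility not binding.

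| What is tested | False early stop | Final test alone | Overall |
|---|---|---|---|
| One contrast | 1.8% | 5.0% | **5.9%** |
| Three-arm chi-squared (2 df) | 1.7% | 5.0% | **5.9%** |
| Either hypnosis arm v control | 3.4% | 9.1–9.2% | 10.7% |
| Any of three pairs | 4.7% | 12.3% | 14.3% |

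With 135 per arm at the end, the overall column reads 5.8%, 5.8%, 10.6% and 14.2%. A normal-theory simulation agrees.

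**3. Where the excess comes from.** One contrast: 5.9 − 5.0 = 0.9 points from the looks. Any pair: 14.3 − 12.3 = 2.0 points from the looks and 12.3 − 5.0 = 7.3 points from unadjusted pairwise testing, which would exist with no interim analysis.

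**4. What restores 5%.**

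- p<0.001 at both looks, 0.05 at the end: 5.0–5.1% for one contrast and for the three-arm test.
- p<0.01 kept at both looks: the final level that holds 5% is about 0.041 for one contrast and about 0.040 for the three-arm test.

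**5. Cost in power.** By the uncorrected formula at 135 per group, final test alone:

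Power = Φ{[0.16·√135 − z·√(2·0.72·0.28)] / √(0.80·0.20 + 0.64·0.36)}

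This gives 84% at 0.05 (z = 1.960) and 82% at 0.041. For the first option, the same simulation with one contrast at 80% v 64% stops at either look in about 51% of trials under p<0.01 and about 23% under p<0.001.

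**The case against.** The strongest reply is that the article nowhere states that the final test is at 0.05. That level is inferred from the sizing sentence and the 95% intervals. A sequential method is cited, the committee has terms of reference, and a reduced final level could stand there or in an analysis plan that is not shown. This is right as far as it goes, and the error figures must stay conditional on a final 0.05. It does not remove the mismatch in what was published: the threshold and the sizing level are both in print, and the sample size makes no allowance for a lower final level.

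Second, a reader might infer that the interim rule drives error to 14%. The documents do not support that. The coded comparison of A, B and C fits a single three-arm test at least as well as a search over pairs. Even on the pairwise reading, most of the excess has nothing to do with the looks. Nor does the article promise a family-wise rate: its 0.05 belongs to one two-group comparison, and whether distinct arms need joint adjustment is debated.

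Third, a reader might object that an early stop would exaggerate the effect. If the truth is 80% v 64%, one contrast crosses p<0.01 at the first look in about 21% of trials, with a mean observed gap of about 28 points. But overestimation after an early stop comes with any efficacy boundary, and the committee makes recommendations rather than stopping automatically. This is not a separate fault of the plan.

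Fourth, the recruitment trigger is minor. Outcomes follow within weeks, and the article does not say that undelivered women would be analysed.

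**Conclusion.** The point holds in a limited form. The published interim rule and the published sizing do not belong to the same design. With a final test at 0.05, overall error is about 5.9% on the two mildest readings (one contrast, or the three-arm test) and higher on the others, so 5% is not held on any of them. The excess due to the looks is about 0.9 points on the mild readings. The figure of about 14% applies only if both the interim rule and the final test are run on every pair, which the text permits but does not state.

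The figures assume equal arms, 80% use under no effect, complete outcomes at each look and no binding futility rule. Binding futility would lower the error somewhat, but without a threshold this cannot be calculated. This is a modest inconsistency that is cheap to correct, not a flaw that undermines the trial.

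**What to change.** 1. **State a matched pair of levels.** Either p<0.001 at both looks with the final test at 0.05 (about 5.0% overall), or p<0.01 at both looks with a final level of about 0.04. The first costs early stops. The second costs about 2 points of power (82% against 84% at 135 per group).
2. **Name the one test to which both levels apply:** a hypnosis v control contrast, or the three-arm test. The named contrast rules out a stop on Group 1 v Group 2 alone. The three-arm test does not do so by itself, because it can reject when only the two hypnosis arms differ. If it is chosen, add that a stop also requires a hypnosis v control difference at the interim level; this can only lower the error. Either way, someone supporting the committee must know which coded group is control.
3. **Trigger the looks at 150 and 300 women with a known primary outcome.** This delays each look by some weeks.
4. **Optional:** read pairwise tests at 0.05 only if the final three-arm test rejects. At 150 per arm with no dilution, power for Group 1 v control falls from about 88% to about 85% if both hypnosis arms are at 64%, and to about 79% if Group 2 is intermediate at 72%. The second figure is below the planned 80%, so this is a choice to weigh rather than a necessary correction.

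Items 1 to 3 need changes to the analysis section and the committee's terms of reference only, with no extra women. They should be settled before the first look.
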